# Assessment of the efficacy of a fatigue management therapy in schizophrenia: study protocol for a randomized, controlled multi-centered study (ENERGY)

**DOI:** 10.1186/s13063-020-04606-6

**Published:** 2020-09-17

**Keywords:** Fatigue, Schizophrenia, Negative symptoms, CBT, Sleep, Microbiota

## Abstract

**Background:**

Fatigue is a well-known common clinical feature of numerous chronic diseases including various forms of cancer, neurological disorders such as multiple sclerosis, and psychiatric disorders. A significant proportion of people with schizophrenia (30–60%) reportedly experience fatigue, which impacts negatively on participation in various activities, including work, study, leisure, and social pursuits. Causes of fatigue in schizophrenia are poorly understood and there are no established treatments. Several evidence-based interventions for fatigue syndrome including psychoeducation, cognitive behavioral therapy, and graded exercise therapy have been shown to be effective in other medical conditions and could be adapted to address fatigue in schizophrenia patients. As there are no psychosocial or pharmacological interventions with proved efficacy for fatigue in schizophrenia, there is an urgent need for the development of strategies to improve fatigue management in schizophrenia.

The aim of this project is to evaluate in a single blind randomized clinical trial the efficacy of a cognitive-behavioral therapy (CBT) intervention compared to treatment as usual (TAU) on fatigue as the main outcome in schizophrenia patients. Clinical symptoms, physical functioning, major cognitive functions, quality of life and functioning, treatment dosage, daily motor activity, biological markers with inflammatory markers are also considered as secondary outcomes.

**Methods/design:**

Two hundred patients meeting the inclusion criteria will be randomized to either of the study arms (intervention or TAU). The ENERGY intervention will be delivered according to a standardized treatment manual comprising six modules addressing fatigue and sleep over 14 individual therapy sessions. The treatment encompasses core CBT principles of psycho-education, behavioral activation, behavioral experiments, cognitive restructuring, problem-solving, and relapse prevention. Sessions will follow the traditional CBT structure of agenda setting, review of homework tasks, and introduction of a new concept/technique with collaborative discussions on how to implement such strategies in the participant’s day-to-day environment. Our primary endpoint will be the severity of fatigue assessed at baseline and at the 9-month follow-up using the “Multidimensional Fatigue Inventory” (MFI).

**Discussion:**

The trial will provide the first test of CBT intervention for fatigue for patients with schizophrenia. This study will also test to what extent the treatment can be implemented in everyday practice.

**Trial registration:**

ClinicalTrials.govNCT04332601. Registered on 10 April 2020.

## Introduction

### Background

Schizophrenia is probably the most debilitating of all the mental health disorders. Rates of schizophrenia are similar from country to country—affecting approximately 0.5 to 1% of the population [1]. People diagnosed with schizophrenia usually experience a combination of symptoms [2]: positive (i.e., hallucinations, delusions), negative (i.e., amotivation, reduced expressed emotions, poor or non-existent social functioning), cognitive (i.e., difficulty concentrating, memory impairments), affective (i.e., depression), and disorganization (i.e., disorganized speech, inappropriate affect). Even if medication is considered as the first-option treatment for positive symptoms and relapses in schizophrenia [3], the proportion of individuals who achieve a clinically meaningful benefit is moderate [4]. This can be partly explained by the fact that no pharmacological treatment has been shown effective in treating negative [5] or cognitive symptoms, which are the major cause of the marked functional disability associated with schizophrenia [6]. In addition, other non-psychiatric clinical conditions which are often not the primary focus of clinicians treating this population may have been overlooked [7].

To date, fatigue in patients with severe mental disorders such as schizophrenia has been poorly studied despite several arguments for further investigation [8]. First, lack of energy, one of the main characteristics of fatigue, is frequently encountered in individuals with schizophrenia. Second, fatigue is a common and severe symptom in sleep disorders [9] and depression [10] which both are commonly observed in individuals with schizophrenia [11]. Third, fatigue and psychiatric disorders frequently occur comorbidly, and fatigue may aggravate current existing psychiatric conditions [12].

#### Gap and research hypothesis

Fatigue is a subjective phenomenon defined as “the awareness of a decreased capacity for physical and/or mental activity due to an imbalance in the availability, utilization, and/or restoration of resources needed to perform activity” [13]. Fatigue is common in psychiatric conditions such as anxiety and depression (25–36%) as well as in chronic medical conditions such as cancer, Parkinson’s disease, and diabetes [14, 15]. Problems concerning fatigue are often overlooked due to their complexity [16]. The overlap in symptomatology between psychiatric disorders and fatigue can make it difficult to disentangle complex comorbidities [7, 12]. Indeed, fatigue in its different manifestations is sometimes perceived as a symptom and sometimes a condition mainly communicated by the affected person, with a severe impact on quality of life and interpersonal relations [14, 16, 17]. As a result, studies of fatigue in patients with psychosis are currently lacking. Yet, several arguments support the need to develop effective interventions for the treatment of fatigue symptoms in these patients. First, fatigue is highly prevalent in schizophrenia, with almost 60% of patients reporting clinically significant levels of fatigue [8]. Second the functional consequences of fatigue include considerable impairment and disability, such as amotivation to engage in physical activity [18], cognitive deficits, reduced social interactions, and poorer functional health [8], pointing to fatigue as an important treatment target. Third, fatigue may worsen current existing psychiatric conditions, particularly negative symptoms including apathy, decreased interest, or sustained attention, which poorly respond to pharmacological and psychological treatment.

#### Originality and innovative aspects of the study

No psychosocial or pharmacological interventions exist with proved efficacy on fatigue in schizophrenia. But several interventions including cognitive behavioral therapy (CBT), sleep hygiene education, and graded exercise therapy are effective in other chronic medical conditions such as stroke or chronic fatigue syndrome. There is an urgent need for the development of strategies to improve fatigue in schizophrenia. Another innovative aspect of our project is to develop an integrative model based on biological and psychological factors underlying fatigue severity in schizophrenia such as sleep disorder but also inflammatory processes and microbiota. Fatigue is common in individuals with a chronic illness with an overriding inflammatory process. Uncontrolled neuro-inflammation by pro-inflammatory cytokines is involved in the pathogenesis of schizophrenia. The intestinal microbiota plays a critical role in the immune response [19], with communication between the microbiota and gut mucosal cells regulating the production of cytokines and chemokines. A management of fatigue could decrease this inflammatory syndrome and thus the bacterial translocation.

### Objectives

#### Primary objective

The primary objective in this study is to assess in a randomized, single blind, multi-centered clinical trial the efficacy of an individual cognitive and behavioral therapy protocol versus TAU, on schizophrenia patients’ fatigue severity with a follow-up at 9 months after inclusion.

#### Secondary objectives

Secondary objectives are to examine change in fatigue score over three time points (inclusion to 3 months to 9 months), according to the study arms. Another objective is to assess at the 9-month follow-up the impact of the intervention on:
Clinical symptoms (positive and negative symptoms, depressive symptoms, insight, sleep)Physical functioningMajor cognitive functions (attention, memory and executive functions)Quality of life and functioningTreatment dosageDaily motor activityBiological markers (weight, abdominal perimeter, blood pressure, heart rate, lipids, inflammatory markers)

### Hypotheses

The primary hypothesis is that:
Compared to the control condition (TAU), ENERGY intervention will lead to a reduction in fatigue severity (at the posttreatment and 9-month follow-up)

The secondary hypotheses are that:
2.Compared to the control condition, ENERGY intervention will lead to reductions in negative symptoms and more particularly amotivation and depression severity and will lead to increases in daily motor activity, physical functioning, quality of life, and sleep (posttreatment, 9-month follow-up).

## Methods: participants, interventions, and outcomes

### Participants

Two hundred individuals with schizophrenia will be recruited in 9 centers. Each participating center will include 20 eligible participants in the study, except for the Montpellier center which will include 40 participants. The study protocol has been approved by the Ethical Committee (CNRIPH: 19.11.29.43226) in accordance with the Helsinki Declaration. Written informed consent will be obtained by all participants. The study report will comply with the Consolidated Standards of Reporting Trials (CONSORT) statement and CONSORT-NPT (non-pharmacologic treatments) statement.

### Eligibility criteria

#### Inclusion criteria

Patients eligible in participating in this study must comply with the following criteria:
Age between 18 and 60 years.Signature of informed consent form. If patients have a tutor, they will have to sign the informed consent form too.Patients with a diagnosis of schizophrenia according to the Diagnostic and Statistical Manual of Mental Disorders 5 (DSM 5) established and validated by the study center’s investigating psychiatrist.Patients with a score at the “Multidimensional Fatigue Inventory” (MFI) greater or equal to 10.Patients with a follow-up in a day hospital at inclusion.Subjects must be able to attend all scheduled visits and to comply with all trial procedures.Participation of the patient must be noted in their medical files.Subjects must be covered by public health insurance.

#### Exclusion inclusion criteria are

Patients will not participate in this study if they meet any of the following criteria:
Subject unable to read and/or write FrenchPlanned long-term stay outside of the study region that prevents compliance with the treatment planPatients with a history of severe brain traumaPatients with a history of neurological pathologyPregnant or breastfeeding patients

### Study design and setting

This ENERGY trial is a two-arm study (ENERGY intervention versus TAU), single blind randomized and controlled clinical trial designed to assess the efficacy of an individual cognitive and behavioral therapy in patients with schizophrenia. We adhered to the Consolidated Standards of Reporting Trials (CONSORT) guidelines in the design of the trial.

Patients meeting all of the inclusion criteria and none of the exclusion criteria will be invited to participate in the study. After signing the informed consent form, they will be randomized into one of the two study arms: ENERGY intervention or TAU.

They will be assessed at baseline over a 1-week period for fatigue, global functioning, symptomatology, sleep, cognitive functioning, and antipsychotic medication. Blood samples will be collected. Patients will be re-assessed 3 months later (corresponding approximately to the end of the ENERGY intervention; if the intervention is delayed, this intermediate assessment will be performed as soon as the intervention is completed and within 15 days of the end of the intervention) and 9 months later (approximately 6 months after the intervention with a delay of 15 days maximum) for fatigue, symptomatology, global functioning, sleep, cognitive functioning, and antipsychotic medication. Blood samples will be collected at each of these assessment times.

This study is multi-centered and will be carried out in 9 of the 10 centers participating in the French national network of schizophrenia expert centers (FondaMental Foundation). Each center will recruit patients to both groups and therefore perform the ENERGY intervention. The following centers will be participating in this study:
Hôpital la Colombière, Centre Hospitalier Universitaire (CHU) de MontpellierCHU de Clermont FerrandHôpital Albert Chenevier, CréteilHôpitaux Universitaires de StrasbourgHôpital Sainte Marguerite, MarseilleHôpital Louis Mourier, ColombesHôpital le Vinatier, LyonCentre Hospitalier Alpes IsèreHôpital Charles Perrens Bordeaux

This study protocol has been reported in accordance with the “SPIRIT 2013 Checklist: Recommended items to address in a clinical trial protocol and related documents” (Additional file 1).

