### Participant timeline

Participants will be assessed at the beginning of the study, then re-assessed 3 months later (corresponding approximately to the end of the ENERGY intervention; if the intervention is delayed, this intermediate assessment will be performed as soon as the intervention is completed and within 15 days of the end of the intervention) and 9 months later (approximately 6 months after the intervention with a delay of 15 days maximum) for fatigue, symptomatology, global functioning, sleep, cognitive functioning, and antipsychotic medication. Blood samples will be collected at each of these assessment times (see Fig. 1).

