### Planned trial calendar

Planned regulatory period: 6 months

Planned duration of recruitment: 36 months

Duration of participation of each subject: 9 months

Planned statistical analysis/valorization period: 6 months

Planned total trial period: 57 months

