### Determination of sample size and power calculation

The main objective is to evaluate the efficacy of a therapeutic protocol for the management of fatigue in schizophrenia patients. The change in fatigue level will be compared 6 months after the intervention (9-month follow-up) between two groups of patients: one following the 3-month individual program for the management of fatigue, and one receiving care as usual. The sample size calculation is based on the change in the general fatigue score, one of the five sub-scales of the Multidimensional Fatigue Inventory (MFI) [29], measured at inclusion and 9 months later.

A study exploring the psychometric properties of the MFI in 93 out-patients with schizophrenia spectrum disorders reported a mean score on the general fatigue subscale of 13.4 (standard deviation (SD): 3.9) [30]. An earlier study reported a mean score of 16 (SD 3.2) for this sub-scale in 166 patients with fibromyalgia and chronic widespread pain [49].

In our study of SZ patients attending a day hospital, with a general fatigue subscale score greater or equal to 10 at study entry, we can expect an average score of approximately 16 (SD 4) on this subscale.

We can also hypothesize a 2-point reduction in the mean score on this sub-scale between the start of the trial and the 9-month follow-up in the group receiving the intervention. No change in the severity of fatigue is expected in the group receiving treatment as usual. Under this effect-size hypothesis, with scores in both groups set at 16 (SD 4) at inclusion, the mean score in the group receiving the intervention is expected to drop to 14. Under the hypothesis of a stable standard deviation of 4 in both groups and at both time points, power set at .085 and alpha at *p* = 0.05, 73 patients per group are necessary.

In order to allow for loses at follow-up (estimated for SZ patients at 15–20% over a 9-month period), it will be necessary to recruit 100 subjects per group.

The 9 centers participating in this study are part of the French network of expert centers in schizophrenia of the FondaMental foundation. Participants will be recruited directly from the day hospitals in each of the centers.

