### Blinding

The psychologists performing inclusion, 3-month, and 9-month assessments will be blind to the allocations of the patients to either study arms of the randomized controlled study (RCT). Patients and psychologists performing the ENERGY therapy will be asked to avoid telling the assessor to which group they/the patient belongs to. A psychologist, blind to the randomization process, will perform the assessments, and another psychologist will perform the therapy interventions. Participants will be asked to not reveal their group allocation to the assessors. The data analysts that will be performing the analyses at the conclusion of the trial will also be blinded as to what group the data corresponds to. Unblinding should occur only in exceptional circumstances in case of any adverse events (AE) which will be reported immediately to the investigator.

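### The 3-month assessment is tied to the end of a therapy that only the ENERGY arm receives, so the arms would tend to be measured at different elapsed times; the 9-month visit has two descriptions that need reconciling

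*Protocol article*

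**What the plan says.** Under Study design and setting, the intermediate visit is introduced as follows: "Patients will be re-assessed 3 months later (corresponding approximately to the end of the ENERGY intervention"). The exception for late therapy follows: "if the intervention is delayed, this intermediate assessment will be performed as soon as the intervention is completed and within 15 days" of its end. Participant timeline repeats it for all participants: "if the intervention is delayed, this intermediate assessment will be performed as soon as the intervention is completed". Biological measures uses the same anchor, placing the second pedometer week directly after therapy for every patient.

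The final visit is described in two ways.

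- Counted from inclusion: the Primary objective has "with a follow-up at 9 months after inclusion", and the Planned trial calendar has "Duration of participation of each subject: 9 months".
- Counted from therapy: Participant timeline has "9 months later (approximately 6 months after the intervention with a delay of 15 days maximum"), and the sample size section has "The change in fatigue level will be compared 6 months after the intervention (9-month follow-up) between two groups of patients".

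Therapy is 14 sessions, one per week (Intervention description). Randomization follows the baseline measurements (Randomization and matching), and baseline takes up to a week (Study design and setting). Under Blinding, "The psychologists performing inclusion, 3-month, and 9-month assessments will be blind to the allocations".

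**The concern.** A visit that waits for therapy to finish has a reference point in one arm only. When therapy runs late, the ENERGY visit moves and the TAU visit has no stated reason to move with it. The 15 days run from the end of therapy, not from month 3, so the shift has no upper limit.

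The analyses directly exposed are those under Secondary endpoint analysis: the change from inclusion to 3 months, and the mixed-effects model over three time points. If nominal visits stand for different elapsed times by arm, any drift over time is mixed with the treatment contrast.

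The primary analysis uses the 9-month visit. Its two descriptions agree only if therapy ends at month 3. If it ends later, a site cannot tell from the text which one governs.

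There is also a possible side effect on blinding. A conspicuously late visit could hint at the arm to an assessor rating interview-based scales such as the PANSS and CAINS.

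**Working it through.** **Inputs.** 14 weekly sessions (Intervention description); visits at 3 and 9 months, with a 15-day allowance after the end of therapy (Study design and setting, Participant timeline); baseline of up to one week, followed by randomization. One month is taken as 365.25/12 = 30.44 days, so 3 months = 91.3 days and 6 months = 182.6 days.

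**The plan's own figure.** Fourteen weekly sessions have 13 intervals: 13 × 7 = 91 days = 2.99 months. The statement that therapy ends at approximately 3 months is therefore reproduced, provided session 1 falls on day 0 of the count.

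**Slack.** 91.3 − 91 = 0.3 days, so in practice there is none. Counted from the start of a one-week baseline, the last session is at 7 + 91 = day 98 even with perfect attendance.

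**Start lag, no missed session.** Last session = lag + 91. Latest intermediate visit = last session + 15. Final visit, if counted from therapy = last session + 182.6 days. The lags are assumptions.

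| Lag (days) | Last session | Latest intermediate visit | Final visit if 6 months after therapy | Same, plus 15 days |
|---|---|---|---|---|
| 0 | day 91 (2.99 months) | day 106 | 8.99 months | 9.48 months |
| 7 | day 98 (3.22) | day 113 | 9.22 | 9.71 |
| 14 | day 105 (3.45) | day 120 | 9.45 | 9.94 |
| 28 | day 119 (3.91) | day 134 | 9.91 | 10.40 |

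The TAU comparators are about day 91 and 9.0 months. In the first row therapy is not late, so day 106 arises only if the 15-day allowance is used anyway.

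**Missed weeks.** The documents give no attendance rate. Assume that each weekly slot after session 1 is attended independently with probability p. Then the mean last-session day = lag + 7 × 13/p, and the chance of missing none of sessions 2 to 14 is p^13.

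| p (assumed) | Chance of no missed week | Mean days past 3 months, no lag | Mean days past 3 months, 7-day lag |
|---|---|---|---|
| 0.95 | 51% | 4.5 | 11.5 |
| 0.90 | 25% | 9.8 | 16.8 |
| 0.80 | 5% | 22.4 | 29.4 |

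The later ENERGY visit is thus of the order of 1 to 4 weeks over most of this range, and its size depends entirely on the assumed lag and attendance.

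**The two descriptions of the final visit.** They coincide if therapy ends at month 3 (3 + 6 = 9). If it ended at month 5, an illustration only, they would give month 5 + 6 = 11 against month 9.

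**The case against.** The best defence is that the 3-month measurement is meant to represent the end of the intervention, as Secondary endpoint analysis says, so waiting for the last session serves that purpose. The visit-schedule figure is not available here, and a journal article may leave TAU windows to the full protocol. Data collection plans each evaluation around the patient's own schedule, so dates may vary in both arms. The sample size section expects no change in fatigue under TAU, and the documents give no time trend or relapse rate that would turn a few weeks into a bias of known size. All of this limits the consequence. It does not remove the problem: the moving rule is printed explicitly, twice, and its reference point exists in one arm only.

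Three stronger readings are tempting and are not supported:

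- A reader might infer that 14 weekly sessions cannot end by 3 months. They can: 91 days against 91.3, and the text says only that the two correspond approximately.
- A reader might infer that the primary visit also moves by arm. Only the intermediate assessment has a moving rule. The objective and the trial calendar fix the final visit at 9 months, and the mention of 6 months after therapy can be read as a gloss, with delay limited to 15 days. The fault is inconsistent wording.
- A reader might infer that the visit date reveals the arm. Nothing says that the assessor books visits or is told when therapy ends; the therapist is a different psychologist, and patients and therapists are asked not to disclose. Site psychologists do help manage the study locally, so a cue is plausible, but it remains an inference. It does not act on the MFI, which patients who know their arm complete themselves.

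**Conclusion.** The point stands in a limited form. The rule for the intermediate assessment has an ENERGY-only anchor, no cap and no TAU counterpart, and the therapy schedule has no slack. Followed as written, it would tend to place the ENERGY visit later than the TAU visit: by about a week with a one-week start lag and perfect attendance, and by up to about 22 days (113 − 91.3) with that lag and the whole 15-day allowance. Missed weeks add to this. These figures assume that TAU is seen at 3 months exactly; the lag and attendance values are assumptions too.

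The effect falls on the 3-month change and the three-time-point model, both secondary. Its size in MFI points cannot be derived from the documents. For the primary visit, the finding is that two descriptions must be reconciled; a shift between arms is not shown. The amendment is worth making, but this does not undermine the primary comparison or the sample size.

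**What to change.** - Time both assessments from one origin in both arms, for example randomization, with the same window, and book them independently of therapy completion.
- State that the 9-month visit is counted from that origin only. Align the Primary objective, Study design and setting, Biological measures (pedometer), Participant timeline, Planned trial calendar and sample size sections accordingly.
- Record the date of the last session and the number of sessions attended.
- Add a sensitivity analysis that uses actual time since randomization.

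The cost is a short amendment and revised visit windows in the eCRF. Therapy and sample size are unchanged. The real price is that some ENERGY patients will have the secondary 3-month assessment before their last session, so it will not always represent the end of therapy; the recorded session data allow this to be described.
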